#### Aim 2 (Neighborhood-Level Outcomes)

The neighborhood is the unit of analysis. The dependent variables are neighborhood-aggregated outcomes (eg, mean collective efficacy scores and rates of crime or violence). The independent variable is treatment assignment. The primary analysis will use an analysis of covariance specification, where the neighborhood-level outcome at follow-up is regressed on treatment assignment and the baseline value of the same outcome. This model provides an adjusted mean difference in follow-up outcomes between intervention and comparison neighborhoods, controlling for baseline heterogeneity. As only 8 clusters are available, models will not include random effects but will instead rely on cluster-robust variance estimators with small-sample corrections. Adjustment for additional neighborhood-level covariates (eg, baseline socioeconomic disadvantage, racial composition, and baseline crime levels) will be included cautiously in sensitivity analyses, given the limited degrees of freedom. These covariates will be added one at a time to assess the robustness of the primary results. Sensitivity analyses will also include difference-in-differences models, where the dependent variable is the change from baseline to follow-up. Results will be expressed as standardized effect sizes for comparability across outcomes and to provide planning parameters for future trials.

#### Missing Data

Missing data will be addressed using full information maximum likelihood in the mixed effects models, which provides unbiased estimates under a missing-at-random assumption. As a sensitivity analysis, multiple imputation by chained equations will also be conducted for key outcomes and covariates. Both approaches preserve variability and prevent the downward bias in SEs that can arise with complete-case analysis. The extent and patterns of missing data will be reported, and the results will be compared across approaches to confirm robustness.

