#### Aim 1 (Individual-Level Outcomes)

The individual is the unit of analysis, but clustering within neighborhoods is explicitly modeled. The independent variable of interest is neighborhood-level treatment assignment, with covariates including baseline individual scores, demographic characteristics (eg, age, sex, race or ethnicity, and education), and relevant neighborhood-level indicators. Continuous dependent variables will be analyzed using linear mixed effects models of the form:

Yij=β0+β1(treatmentj)+β2(baselineYij)+β3Xij+uj+εij,

where YijY_{ij}Yij is the outcome for individual iii in neighborhood jjj, XijX_{ij}Xij are individual covariates, uju_juj is a random intercept for neighborhood, and εij\varepsilon_{ij}εij is the individual-level error term. The random intercept uju_juj captures unobserved contextual influences shared by individuals in the same neighborhood (eg, social environment, policing, or community resources). By including uju_juj, the model allows each neighborhood to have its own baseline level of the outcome, and treatment effects are estimated net of this shared clustering. For binary dependent variables (eg, presence or absence of exposure to violence), generalized linear mixed models with a logit link will be used, also including a neighborhood random intercept.

The intercept term represents the expected outcome value when predictors are set to 0 (or to reference categories). In the context of these analyses, a random intercept for neighborhood allows the model to adjust for systematic differences between neighborhoods not explained by observed covariates. This ensures that individuals are not treated as statistically independent when they belong to the same neighborhood and that SEs correctly reflect the clustered design. Fixed intercepts anchor the regression line, providing the baseline level against which covariate and treatment effects are interpreted.

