The study also has limitations related to participant retention, measurement, and sampling. Two factors limit retention and, relatedly, data missingness. First, as a community-based study recruiting participants with multiple structural barriers to participation, including transportation, retention of this cohort remains a critical challenge, with the most vulnerable at especially high risk for loss to follow-up. Thus, there will likely be significant nonrandom missing data. The study team makes every effort to reach out to participants and reduce barriers to participation (eg, delivering paper surveys to their home). It is important to note that participants in the intervention training sessions are asked to attend all the sessions and are given an additional US $25 if they meet this goal. This additional payment helps with retention in the training sessions. However, additional participants cannot join after the second session. In comparison sites, participants can attend any or all the health sessions and can start attending any session, resulting in more total participants in the health sessions.

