Participant surveys are collected anonymously, with each participant creating their own personal identification code that only they know to match surveys over time. Such user-identified codes are effective at deidentification and therefore reduce bias, such as social desirability responding. However, they also limit data analysis to those participants for whom records can be matched. We attempt to address this problem using a detailed matching algorithm across sites and time points [40]. We will conduct several sensitivity analyses to assess impact on results (see *Methods*). Second, 2 issues may affect data quality. Different modes of delivery (researcher and self) and formats (oral, paper, and online) are used for participant and community surveys. These differences in administration and instrumentation can threaten measurement validity by introducing unintended sources of response variation. In addition, secondary outcome measures (willingness to intervene, social connectedness, and norms, values, and attitudes about intervening) have not been formally validated. However, prior studies suggest criterion validity for these measures, finding intervention-related gains pre- and post-participation [10,48]. We will analyze the association of these measures with related and unrelated measures and conduct subgroup analyses with data from this study to strengthen confidence in measurement validity. Finally, the study cannot overcome limitations related to availability sampling of participants, as is common in similar interventional studies. However, the study takes an important step toward enhancing causal validity (via propensity score matching of neighborhoods), and thus, threats to generalizability engendered via availability sampling should minimally be accompanied by selection bias.

On the basis of neighborhood uptake and participant recruitment, intervention training sessions and health topic sessions are acceptable at a neighborhood and individual level and recruitment is feasible. The strong partnerships previously established with key stakeholders in each site facilitate neighborhood uptake and participant recruitment. Furthermore, participant and community surveys can be feasibly administered. Neighborhoods selected for the study reflect the intended neighborhoods and residents, that is, predominately BIPOC (Black, Indigenous and People of Color), low socioeconomic status facing multiple challenges, including violence.

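### As written, the Aim 1 model makes FIML a complete-case analysis for missing outcomes, and comparing it with a second missing-at-random method cannot confirm robustness to the nonrandom loss the authors think likely

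*Protocol article*

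**What the plan says.** Four places in the protocol article bear on this point.

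- **Outcome Measures, Primary Outcome Measure**, defines the primary outcome as individual collective efficacy at T1, T2 and T3.
- **Aim 1 (Individual-Level Outcomes)** gives one model: "Continuous dependent variables will be analyzed using linear mixed effects models of the form" Y_ij = β0 + β1·treatment_j + β2·baselineY_ij + β3·X_ij + u_j + ε_ij. The indices are person and neighborhood only, the single random effect is for neighborhood, and baseline is a covariate.
- **Missing Data** states: "Missing data will be addressed using full information maximum likelihood in the mixed effects models, which provides unbiased estimates under a missing-at-random assumption". It adds: "As a sensitivity analysis, multiple imputation by chained equations will also be conducted for key outcomes and covariates". It says of the two methods: "Both approaches preserve variability and prevent the downward bias in SEs that can arise with complete-case analysis". It then says that "the results will be compared across approaches to confirm robustness".
- **Discussion (limitations)** expects the most vulnerable participants to be lost and concludes: "Thus, there will likely be significant nonrandom missing data". It adds that self-created survey codes restrict analysis to records that can be matched, and promises, with a pointer to Methods: "We will conduct several sensitivity analyses to assess impact on results".

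**The concern.** The stated method, its claimed benefit and the expected threat do not fit together. FIML improves on complete cases when a person's other outcome measurements enter the likelihood. In the written model there are none: T1 is a covariate and T2 does not appear. The missing-data check then compares two methods that share the MAR assumption, although the article itself expects loss that may break it.

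The Analytic Approach section puts its emphasis on estimation and magnitude, so bias in the estimate matters more than the outcome of a test. Loss may also differ between arms by design. The CRCEI sites pay a bonus for full attendance and close entry after session 2, while the comparison sites let people join and attend any session.

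**Working it through.** **1. The plan's own figure.** Inputs from Results and Sample Size and Power: 111 and 151 participants, 4 neighborhoods per arm, two-sided alpha 0.05, 6 df, 80% power.

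MDES = (t_0.975,6 + z_0.80) × √(DE1/111 + DE2/151), with DE = 1 + (n_arm/4 − 1)·ICC and t + z = 2.447 + 0.842 = 3.289.

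- ICC 0.05: DE1 = 1 + 26.75 × 0.05 = 2.34, DE2 = 1 + 36.75 × 0.05 = 2.84, SE = 0.1996, MDES = 0.656.
- ICC 0.10: 0.832.
- ICC 0.20: 1.103.

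These match the stated 0.66, 0.83 and 1.10, so those figures assume all 262 participants supply an outcome. With 70% retained (183 people) they become 0.71, 0.87 and 1.13.

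**2. FIML under the written model.** For neighborhood j, the likelihood with missing outcomes integrated out is ∫ f(Y_obs, Y_mis | X) dY_mis = f(Y_obs | X_obs). For a multivariate normal this simply deletes the rows with no outcome, which leaves the complete-case likelihood. Estimates and SEs are therefore the same. A fit to simulated data (262 people, 8 clusters, 30% of outcomes missing) shows it: treatment effect 0.0092 and baseline slope 0.4819 both ways. The result comes from the algebra; the fit only illustrates it.

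**3. Size of the bias.** The documents give no attrition rate, so every setting here is an assumption. The true effect is zero and score-related dropout occurs in one arm only. The strong setting uses 400,000 people and 32% loss, with log-odds of dropout changing by 1.2 per point of score. It has T2-T3 correlation 0.60/√(0.86 × 0.97) = 0.66 and T1-T3 correlation 0.50/√0.97 = 0.51. The milder settings have about 30% loss; for the T2 row they use correlations 0.6-0.7 and log-odds 0.5-1.0 per SD. Absolute bias in SD units:

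| Loss depends on | Setting | FIML = complete case | Imputation on model covariates only | Method using T2 |
|---|---|---|---|---|
| T1 | strong | 0.00 | 0.00 | 0.00 |
| T2 | milder | 0.03-0.06 | not run | 0.00-0.01 |
| T2 | strong | 0.10 | 0.10 | 0.00 |
| unseen T3 | milder | 0.09-0.18 | not run | 0.07-0.16 |
| unseen T3 | strong | 0.24 | 0.24 | 0.19 |

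The sign depends on which arm loses its low scorers.

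**4. Hand check of the nonrandom rows.** If dropouts in one arm score δ SD lower after adjustment for baseline and covariates, bias = loss share × δ. Then 0.30 × 0.3 = 0.09 and 0.40 × 0.5 = 0.20.

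**5. What the planned comparison can show.** If imputation uses only the model's covariates, it repeats FIML in every row where it was run, and agreement is built in. If it uses T2, it can expose loss that depends on T2. When loss depends on T3, the two methods differ by only 0.24 − 0.19 = 0.05 SD in the strong setting, and both are wrong in the same direction.

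**6. The pointer to Methods.** The sensitivity analyses named there are chained-equations imputation (Missing Data) and, under Aim 2, added covariates and difference-in-differences. None is described as dealing with unmatched codes.

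**The case against.** - **The equation is a template in a condensed article.** A repeated-measures model may be intended, since the outcome is defined at three times, and FIML would then use T2. This is possible, but the written equation does not say so and does not state whether Y is T2 or T3. It needs correcting on either reading.
- **A nonrandom-missingness analysis can be left to the SAP.** True, and its absence alone would be no finding. The article, however, fixes the comparison and states what it will establish, and that claim goes too far.
- **The FIML sentence is correct as statistics.** It is: under MAR given the modelled covariates the estimate is unbiased, as the T1 row shows. What fails is the claimed advantage over complete cases for missing outcomes, and any protection against nonrandom loss.

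A reader might also infer more than the documents support:

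- *That FIML drops anyone with a missing T1.* The identity covers missing outcomes. FIML that models covariates jointly can keep people with a missing covariate, and Results reports that all 262 completed baseline.
- *That T2 is never used.* The article says "multiple imputation by chained equations will also be conducted for key outcomes and covariates", and T2 collective efficacy may be among those outcomes. T2 is absent from the primary model only.
- *That the article says MAR will fail.* It says nonrandom loss is likely. The word may mean no more than not completely at random, and loss explained by measured covariates is compatible with MAR.
- *That Methods has nothing behind the pointer.* It may refer to the Missing Data section, since an unmatched follow-up is missing data. Even so, several analyses are promised and one relevant one is visible.

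**Conclusion.** The point holds in this limited form. Under the Aim 1 equation as written, FIML equals complete cases for missing outcomes and T2 does not inform T3. Agreement between FIML and chained-equations imputation would show robustness within MAR only.

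With about 30% loss and score-related dropout in one arm, the bias is about 0.03-0.10 SD if loss depends on T2, and it vanishes when T2 is used. It is about 0.1-0.2 SD if loss depends on the unseen T3 score (0.09-0.24 across the settings run), of which roughly four fifths or more remains with T2. For scale, 0.09-0.20 is 14-30% of the smallest stated detectable effect (0.09/0.66 and 0.20/0.66). It is also smaller than the unadjusted 95% half-width at ICC 0.05, 2.447 × 0.1996 = 0.49.

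The bias is therefore moderate and conditional on assumed attrition, and it is close to zero if loss depends only on modelled covariates. The change should be made because it is cheap and because the plan claims a protection that its check cannot give.

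**What to change.** 1. Write the Aim 1 model for continuous outcomes as a repeated-measures mixed model of T2 and T3, with T1 as covariate, time, treatment-by-time, and random intercepts for participant and neighborhood. Name one time point as the primary contrast.
2. State that T2 is in the chained-equations imputation model.
3. Add delta-adjusted multiple imputation by arm, for example shifting imputed scores by 0.1 to 0.5 SD, and report the shift at which the conclusion changes.
4. Limit the robustness claim in Missing Data to robustness within MAR. Make the Discussion's pointer lead to a stated analysis of unmatched survey codes.

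A neighborhood-by-time random effect is not advisable, because eight clusters would estimate it poorly. A model that keeps unlinked surveys is not needed either; it would enter one person's T1 and T3 as two people.

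The cost is some analysis code, a paragraph of text and one added modelling assumption (the within-person correlation structure), with no new data. Results dates the start of analysis for aims 1 and 2 to April 2026, so the change should be dated, with a note of whether outcomes by arm had been seen.

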### Process Evaluation Analytic Methods

A mixed methods convergent approach is taken to analyze process data across quantitative and qualitative sources [42] (see Table 3 for a full description of implementation dimensions and data). This approach involves concurrent analysis of quantitative and qualitative data. Specifically, basic descriptive statistics are used to quantitatively describe implementation across intervention sites and to indicate fidelity or lack of fidelity to core program components. Simultaneously, qualitative data are integrated across sources, analyzed using Willig et al’s 6-step approach to thematic analysis [42-47] and integrated into quantitative results on an ongoing basis. Dedoose is used to organize, code, memo, and visualize qualitative and quantitative process data. Bringing both quantitative and qualitative findings together, implementation indicators are verified across data sources and quantitative findings are explained in more depth by findings from qualitative analyses. Visual tools, including joint displays of qualitative and quantitative data, are used as an analytic aid [45], especially in identifying patterns and unique cases. All findings related to implementation indicators are tracked in an implementation matrix that was collaboratively designed by the second author and intervention team [47]. In alignment with principles of data justice and guidance on enhancing trustworthiness in qualitative research [13,37], findings are verified on an ongoing basis and via discussion with research team members, intervention and comparison team members, and participants (in interviews and steering committee meetings).

**Table 3. T3:** Process and implementation outcomes for the intervention sites.

Implementation construct	Dimensions	Definition	Data sources	Timing
Fidelity: whether and how the intervention is implemented as intended	Phase 1 Fidelity	Whether and how phase 1 is implemented as intended	Session observation forms and memos	Each session in phase 2
	Phase 2 Fidelity	Whether and how phase 2 is implemented as intended	Team event calendar	Ongoing
	Phase 3 Fidelity	Whether and how phase 3 is implemented as intended	Facilitator interviews	Between phases 2 and 3
	Global fidelity	Whether and how the intervention is implemented as intended overall	CE^a^ team interviews Fidelity matrix Semistructured field notes and memos	Implementation midpoint and end Ongoing All programmatic meetings
Adaptations: modifications made to the intervention as designed to better fit the setting’s needs, preferences, or other important characteristics, as well as motivations; also speaks to differentiation across sites	Phase 1 Adaptations	Planned and unplanned modifications to the intervention in phase 1	Session observation forms and memos	Each session in phase 2
	Phase 2 Adaptations	Planned and unplanned modifications to the intervention in phase 2	Facilitator interviews	Between phases 2 and 3
	Phase 3 Adaptations	Planned and unplanned modifications to the intervention in phase 3	CE team interviews	Implementation midpoint and end
	General Adaptations	Planned and unplanned modifications to the intervention that span phases	Semistructured field notes and memos	All programmatic meetings
Responsiveness: the degree to which and ways participants engage/participate in, are satisfied with, and demonstrate or express uptake of content	Engagement (phase 2)	The degree to which and ways in which session content and delivery involved participants during and across sessions, includes indication of lack of engagement during sessions or missing sessions, and sentiments of inclusion or exclusion expressed by participants	Session observation forms and memos Feedback questionnaires Participant and facilitator interviews	Sessions in phase 2 Sessions in phase 2 Between phases 2 and 3
	Satisfaction (phase 2)	The degree to which participants and facilitators are satisfied with sessions	Feedback questionnaires	Each session in phase 2
	Sources of satisfaction	The elements of the program participants and facilitators enjoyed or otherwise met or exceeded expectations	Participant and facilitator interviews	Between phases 2 and 3
	Uptake of intervention content	Perceived or observed change among participants, facilitators, and the community in relation to intervention	Session observation forms and memos Participant and facilitator interviews	Each session in phase 2 Between phases 2 and 3
Reach: the proportion of participants that meet inclusion criteria, the representativeness of participants to the target population (e,eg, end users of the intervention) that accepts and uses the intervention (Durlak 2010), and the match between who participates; also includes perceptions of the ideal target population	Acceptance	The number of facilitators and participants recruited and proportion youth versus adults	Participant survey Facilitator contracts	T1 Phase 1
	Participant relevance	The proportion of participants and facilitators that meet inclusion criteria and reflect the broader neighborhood population Perceived facilitator and participant relevance to the target population	Participant survey Facilitator contracts CE team interviews US Census 2020 Participant and facilitator interviews CE team interviews	T1 Phase 1 Implementation midpoint and end NA Between phases 2 and 3 Implementation midpoint and end
	Meeting attendance	Participation of facilitators and participants in phase 1 (facilitators only), phase 2 (facilitators only), and phase 3 team and planning meetings, for youth and adults	Payment records Team event calendar	Ongoing Ongoing
	Session attendance	The number of sessions attended per participant and facilitator, youth, and adults	Attendance records Payment records CE team interviews	Phase 2 Ongoing Implementation midpoint and end
		Barriers to and facilitators of attendance	Participant and facilitator interviews CE team interviews	Between phases 2 and 3 Implementation midpoint and end
	Community reach	The number of households that participated in the community survey	Community surveys Community surveys	Phase 1 start and phase 3 end Phase 1 start and phase 3 end
		The number of invited speakers and service providing and other organization representatives that attended phase 2	Session observation forms and memos	Phase 2
		The number of community members who participated in or were touched by the phase 3 project and how	Attendance records	Phase 3
Dosage: how much intervention was delivered	Phase 1 Dosage	The number of community engagement activities conducted or events attended The number of phase 1 meetings held with facilitators and participants (phase 3 only) The number of community engagement activities (phase 1) conducted or events attended by a team member The number of households invited to participate in the community survey in phase 1	Team event calendar Team event calendar and payment records Team event calendar Community survey tracking forms	Phase 1 Phase 1 Phase 1 Phase 1 start and Phase 3 end
	Phase 2 Dosage	The number of training sessions held The number of phase 2 meetings held with facilitators	Session observation forms and memos Team event calendar and payment records	Phase 2 Phase 2
	Phase 3 Dosage	The number of planning meetings held with community members and facilitators The number of hours phase 3 project was implemented for and by community members	Team event calendar and payment records Team event calendar and payment records	Phase 3 Phase 3
Qualities and differentiation: features of implementation and the context that make each site unique	Neighborhood context	Social and economic conditions in the neighborhood	US Census Police violent crime incidence data Community survey memos CE team interviews Participant and facilitator interviews	2020 Monthly Phase 1, phase 3 Implementation midpoint and end Between phases 2 and 3
	Organizational context	Focus, size, structure, and other characteristics of partner organization	Semistructured field notes and memos CE team interviews Participant and facilitator interviews	Ongoing Implementation midpoint and end Between phases 2 and 3
	Significant events w/in sessions and group dynamics	Significant moments of conflict, celebration, and learning	Session observation forms and memos CE team interviews Participant and facilitator interviews	Phase 2 Implementation midpoint and end Between phases 2 and 3
	Significant events in the community	Significant crime, violence, or other events occurring in the community	Semistructured field notes and memos Session observation forms and memos CE team interviews Participant and facilitator interviews	Ongoing Phase 2 Implementation midpoint and end Between phases 2 and 3
	Competing interventions	Discussion or observation of other community-building and violence prevention interventions in the community	Session observation forms and memos Semistructured field notes and memos CE team interviews Participant and facilitator interviews	Phase 2 Ongoing Implementation midpoint and end Between phases 2 and 3

a CE: collective efficacy.

